The primary objective of this study is to define extent of endothelial dysfunction by noninvasive evaluation for impairment of macrovascular and microvascular endothelial function in children with NS versus healthy controls, by assessment of brachial artery Flow mediated dilation (FMD) and cutaneous post-occlusive reactive hyperemia (PORH), respectively. Secondary objectives includes (a) To prospectively evaluate the temporal course of progression of endothelial dysfunction over 24 months of follow-up of these children in the macrovascular and microvascular endothelium as defined by repeating brachial artery FMD and cutaneous PORH (b) To evaluate in these children the association between endothelial dysfunction and morphological markers of subclinical cardiovascular comorbidity, defined by measurement of carotid intima media thickness (cIMT) and abnormalities on Nail Fold Capillaroscopy (NFC) and echocardiography (c) To look for numerical abnormality of circulating angiogenic cells and micro-particles as a marker of endothelial dysfunction in children with NS versus healthy controls, and (d) To assess biochemical marker of endothelial dysfunction in children with NS versus healthy controls.

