##### Endpoint

The primary endpoint will be the peak hyperaemia after the cuff release over the skin of volar aspect of forearm. In addition, area under the hyperaemic curve (AUCh), the raw value of the peak minus biological zero, increase in post-ischemic flow using area under the curve at baseline and post-ischemia will also be measured.II.Macrovascular Endothelial Function

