### Sample size calculation

Sample size calculation was based upon the reported differences in mean brachial artery FMD and cIMTs in children below 18 years of age in published literature [18] as well as our previous unpublished study in 52 children with NS and 50 healthy controls which looked at cIMT and FMD as the primary outcomes [19]. FMD and cIMT are the most validated indices of endothelial dysfunction and subclinical atherosclerosis in published literature [18]. Data on LDF for PORH in children remains limited. Reported values of mean (± SD) change from baseline of FMD in normal children between 9 and 16 years have ranged between 4.73 ± 4.38% to 7.7 ± 4.0% while the reported maximum mean cIMT in normal children below 18 years of age has been 0.50 + − 0.05 mm3.A.For Cross Sectional Comparisons during Phase I and II

Assuming a conservative estimate of minimum difference of FMD of 3% between normal and nephrotic syndrome with a standard deviation (SD) of 5%, a minimum of 46 cases each of NS and healthy controls will be required for a study with power of 80% at a two-sided 0.05 significance level. This sample size will be able to detect a difference of 0.03 mm of cIMT between children with NS and healthy controls with a power of 80% at a 0.05 significance level. With a 5% attrition rate due to mortality or loss to follow up for the entire study, a minimum sample size of 50 children with NS and 50 healthy children is proposed during phase I of the study. Any subsequent cases of incident/prevalent nephrotic syndrome presenting to the OPD after the 12 months recruitment phase gets over will also be added onto the repository for future analysis. Hence at end of 36 months of study, a minimum of 70 cases each of SSNS, SRNS and healthy controls will be required after final classification of phenotype of NS for a post-hoc Bonferroni adjustment for comparison of 3 means (2 groups of SSNS and SRNS compared to a control healthy group) of FMD and cIMT. Between the 2 participating institutions this number is expected to be available by 36 months of study.B.For Prospective Follow-Up during Phase II

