### Statistical analysis

Descriptive statistics will be used to characterize the entire population and subgroups of interest at baseline and follow-up. Summary statistics such as means, medians, standard deviations and ranges will be used to describe continuous variables, and frequencies will be tabulated for categorical variables. For outcomes collected longitudinally, Kaplan Meier survival curves, scatter plots and grouped box plots will be used to examine assumptions of survival free of adverse outcome or relapses, and linearity and symmetry of data. Repeated measures analysis will be applied for data derived at multiple time points for same child to study correlation with extent and duration of proteinuria. Cox regression analysis will be applied to analyze the time to event data of the primary or secondary endpoints collected in both cohorts of NS and healthy children and assess association of the outcome hazard with clinical covariates of interest. Correlation of markers of endothelial dysfunction and cIMT will be done with extent and duration of proteinuria as defined by the status of remission and number of relapses per year. cIMT will be used as the gold standard for subclinical vasculopathy for evaluation of association with progression of endothelial function. IMT is chosen for diagnostic evaluation study for other biomarkers of cardiovasculopathy since it is the most well characterized surrogate marker of subclinical atherosclerosis. *P*-value < 0.05 will be considered as significant. Statistical analysis will be performed using SPSS Version 17.0.

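### The primary measures are FMD and PORH, but the sample size and the Bonferroni adjustment are attached to FMD and cIMT, and no rule joins the two primary measures

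*Protocol article*

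**What the plan says.** All references are to the Protocol article.

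- **Objectives (last paragraph of the Background).** The primary objective is to define impairment of macrovascular and microvascular endothelial function in NS against healthy controls, "by assessment of brachial artery Flow mediated dilation (FMD) and cutaneous post-occlusive reactive hyperemia (PORH), respectively". cIMT appears under secondary objective (b), among the "morphological markers of subclinical cardiovascular comorbidity, defined by measurement of carotid intima media thickness (cIMT").
- **Specific protocols, microvascular function, Endpoint.** For PORH, "The primary endpoint will be the peak hyperaemia after the cuff release over the skin of volar aspect of forearm".
- **Sample size calculation, opening.** "Sample size calculation was based upon the reported differences in mean brachial artery FMD and cIMTs in children below 18 years of age", together with an unpublished study by the same group. On PORH it says only: "Data on LDF for PORH in children remains limited".
- **Sample size calculation, part A.** The FMD assumption is a "minimum difference of FMD of 3% between normal and nephrotic syndrome with a standard deviation (SD) of 5" percent, giving 46 per group at 80% power and two-sided 0.05. The same size is said to detect 0.03 mm of cIMT. A minimum of 70 per group (SSNS, SRNS, controls) is then required, the stated reason being: "post-hoc Bonferroni adjustment for comparison of 3 means (2 groups of SSNS and SRNS compared to a control healthy group) of FMD and cIMT".
- **Statistical analysis.** A P-value "< 0.05 will be considered as significant", with no distinction between outcomes.

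**The concern.** The outcomes declared primary and the outcomes that the design protects are different pairs. PORH is half of the primary objective, yet it has neither a sizing assumption nor a place in the stated adjustment. cIMT is secondary and has both. The article also gives no ranking of FMD and PORH, no split of alpha between them, and no statement of whether one or both must be significant.

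The error rate attached to the primary claim is therefore undefined. On one natural reading, the study could report impaired endothelial function on PORH alone. That is the measure it was not sized for, and it would be tested at an unadjusted 5% in each of two NS groups.

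**Working it through.** **1. The plan's own figure.** Inputs from part A of Sample size calculation: FMD difference 3, SD 5, two-sided 0.05, power 80%.

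n per group = 2(z₀.₉₇₅ + z₀.₈₀)² × SD²/difference² = 2 × (1.960 + 0.842)² × 25/9 = 43.6, so 44. The t-test version gives 45. The plan states 46, at which power is 82% (normal) or 81% (t-test). The FMD figure reproduces. cIMT at 0.03 mm, with the SD of 0.05 mm reported for normal children, has the same standardised effect of 0.6 and so the same result. No such calculation is possible for PORH, because no difference or SD is given.

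**2. What the 70 per group tells us.** No power is stated for it. It fits alpha 0.05/2 at 90% power (69 normal, 71 t-test) and also alpha 0.05/6 at 80% power (68 normal, 70 t-test). The number therefore does not settle how many tests the Bonferroni sentence is meant to span.

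**3. PORH alone.** Two comparisons with controls, each at 0.05: if independent, 1 − 0.95² = 9.75%. Allowing for the shared control group (simulation, two million draws of three group means), 9.1%.

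**4. FMD and PORH together, if either alone counts.** The FMD-PORH correlation is not in the document, so 0 to 0.8 is assumed.

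| Situation | Independent tests | Simulated, correlation 0 / 0.3 / 0.5 / 0.8 |
|---|---|---|
| Pooled NS against controls, both at 0.05 | 1 − 0.95² = 9.75% | 9.7 / 9.5 / 9.1 / 7.9% |
| SSNS and SRNS each against controls, FMD at 0.025, PORH at 0.05 | 1 − 0.975² × 0.95² = 14.2% | 13.3 / 13.1 / 12.5 / 11.1% |
| As above, but FMD at 0.0125 because the adjustment also spans cIMT | 1 − 0.9875² × 0.95² = 12.0% | 11.2 / 11.1 / 10.7 / 9.8% |

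The second row follows the article's wording most closely. The simulated values in that row allow for the shared control group.

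**5. If both measures must be significant.** There is then no inflation across outcomes. With neither measure truly affected and independent tests, a pooled comparison gives 0.05 × 0.05 = 0.25%. But power for that joint claim cannot be computed without a PORH assumption.

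**6. Four tests in one family.** FMD and PORH, two comparisons each, all at 0.05/4 = 0.0125: simulated family error is 3.9-4.7% over the same correlations. FMD power at 70 per group is Φ(0.6 × √35 − z):
- at 0.05/2: Φ(3.550 − 2.241) = 90.5% (t-test 89.9%)
- at 0.05/4: Φ(3.550 − 2.498) = 85.4% (t-test 84.4%)

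Eighty percent power at 0.05/4 needs 62 per group (normal) or 64 (t-test), fewer than the planned 70.

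**The case against.** The best defence has four parts.

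- **PORH could not be sized, and the article says so.** This stands as far as sizing goes, and the Discussion adds that normative flux data do not yet exist. It does not explain why PORH is absent from the adjustment, since Bonferroni needs no effect size.
- **The Bonferroni phrase sits in a sample size section and may name only the outcomes with sizing data.** This partly stands. No PORH test is described, so a reader might infer that PORH will be tested unprotected, but the article does not say that. Nor does it show that alpha is taken from FMD to pay for cIMT: the phrase concerns three group means and does not clearly divide alpha among outcomes.
- **Alpha allocation and success rules usually belong in an analysis plan, and this is a condensed article.** That would answer a complaint about silence alone. Here, the article does state a sizing basis and an adjustment, and ties both to a pair that differs from its own primary pair.
- **FMD and PORH may be two separate questions, macrovascular and microvascular, in an observational cohort.** This is a fair reading, and adjusting across them is then debatable. The roughly 9% for PORH over two comparisons would remain.

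A reader might also infer a family error of 15-17%. The document does not support it. About 16-17% (correlation 0 to 0.5) requires all four comparisons with controls to be uncorrected, against the planned adjustment of FMD. About 15-16% requires all three pairwise comparisons, including SSNS against SRNS, whereas the text specifies two groups against controls.

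**Conclusion.** The point holds as a mismatch within the article: FMD and PORH are primary, FMD and cIMT are sized and adjusted, and no decision rule joins the two primary measures.

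The sizes are conditional:
- The 9% for PORH assumes that it is tested at 0.05 in each NS group.
- The 9-10% (pooled; 7.9% at correlation 0.8) and the 11-13% (two NS groups) also assume that either measure alone supports the primary claim, which the article neither states nor excludes.
- If both must be significant, the problem changes from inflation across outcomes to a joint claim with no stated power.

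Each reading leaves something to settle before analysis. The weakness lies in how the primary claim is defined; the FMD sample size itself reproduces.

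**What to change.** In part A of Sample size calculation:

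1. Apply the multiplicity adjustment to the declared primary measures, FMD and peak PORH, for SSNS against controls and SRNS against controls. That is four tests, by Holm or Bonferroni at two-sided 0.05 overall.
2. State the decision rule: whether one or both measures must be significant for the primary claim.
3. Treat cIMT as secondary and outside this family, in line with the objectives.
4. State that, among the primary measures, the study is sized for FMD only and that no powered difference is claimed for PORH.

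The cost is wording plus some FMD power. At 70 per group (difference 3%, SD 5%), it falls from about 90% at 0.05/2 to about 84% at 0.05/4, still above 80%. Holm does at least as well as Bonferroni. No further children or measurements are needed.

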For the phase 2 of study with prospective follow up for progression of endothelial dysfunction towards subclinical atherosclerosis as determined by cIMT as the gold standard, if total of 95 children (NS and controls) were to be followed for 24 months after an accrual period of 12 months, assuming a median time of 12 months for a detectable difference of cIMT of > 0.004 mm over 12 months between children with NS and healthy controls, the probability is 80% that the study will detect a difference at a two sided 5.0% significance level, if the true hazard ratio is 2.0. With these preceding assumptions again minimum of 50 children with NS and 50 healthy controls will need to be recruited and followed up over 24 months.

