### Strategies to minimize losses to follow-up

All the patients will be followed up at 12 and 24 months after the baseline assessments. To minimize the risk of retrieval bias, two to five telephone numbers (both mobile and landline) along with their army service number will be noted from the patients or his/her relatives at the time of recruitment. A trained research worker will attempt to contact the participants one month, one week and two days prior to their respective follow up.

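### The Phase II power statement (95 children, 80% at HR 2.0) is built on 24 months after a 12-month accrual, but each child stops at 24 months; on the reading that reproduces 95 under that scheme, power is about 75–76%

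*Protocol article*

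**What the plan says.** The Phase II part of Sample size calculation sets the observation scheme as "if total of 95 children (NS and controls) were to be followed for 24 months after an accrual period of 12 months". The other inputs are a single median, "assuming a median time of 12 months for a detectable difference of cIMT of > 0.004 mm over 12 months", and an effect size, "if the true hazard ratio is 2.0". The claim is that "the probability is 80% that the study will detect a difference at a two sided 5.0% significance level". The section concludes that a "minimum of 50 children with NS and 50 healthy controls will need to be recruited and followed up over 24 months". The Phase I part of the same section gives the loss allowance: "With a 5% attrition rate due to mortality or loss to follow up for the entire study". Taking 5% from 100 children leaves the 95 used in Phase II.

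The schedule appears in four other places. Strategies to minimize losses to follow-up says: "All the patients will be followed up at 12 and 24 months after the baseline assessments". The abstract's Methods give the same two time points. The inclusion criteria ask families to commit to 24 months. The Phase ii section reclassifies each case 24 months after that case's own recruitment and takes samples at baseline, 12 and 24 months. No visit after month 24 is described. Statistical analysis names Cox regression for time-to-event endpoints.

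**The concern.** In a survival sample size, an accrual period followed by further follow-up means that everyone is observed until a common closing date. With 12 months of accrual and 24 months after it, the first child contributes 36 months, the last contributes 24, and the average is 30. If each child instead stops at 24 months, fewer events occur among the same 95 children, and the stated 80% no longer describes the study being run.

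There is also a smaller issue. Progression of carotid intima media thickness (cIMT) can be seen only at the 12- and 24-month visits, so every such event falls at one of two times, whereas the calculation treats event times as continuous.

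What is at stake is the power claim that supports the 50 + 50 minimum for Phase II, which serves a secondary objective.

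**Working it through.** **Inputs from Sample size calculation.** HR 2.0; two-sided 5%; 80% power; 1:1 allocation; 95 children after 5% loss from 100; one median of 12 months, group not named; 12 months accrual plus 24 months. **Assumptions of this check.** Exponential event times, uniform accrual, and the assignment of the 12-month median, which is varied below.

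**Step 1. Events needed (Schoenfeld).** d = 4 × (1.96 + 0.8416)² / (ln 2)² = 65.3.

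**Step 2. Reproducing 95 under 12 + 24 months.** The event probability is p = 1 − [exp(−24λ) − exp(−36λ)] / (12λ).
- NS, median 12 (λ = ln 2/12): p = 1 − (0.25 − 0.125)/0.693 = 0.820.
- Controls, median 24 (λ = ln 2/24): p = 1 − (0.5 − 0.354)/0.347 = 0.577.
- Mean 0.699, so N = 65.3/0.699 = 93.5. With 95 children there are 66.4 events, and power = Φ(√66.4 × ln 2/2 − 1.96) = 80.6%.

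Two close variants give N = 96.4 (unequal-variance log hazard ratio) and 95.8 (one average median of 18 months). Freedman's formula gives 101 and Lachin–Foulkes 99, which fit less well. Under the same accrual scheme, a pooled 12-month median gives N = 81 to 88, and a 12-month median in controls (6 in NS) gives 73 to 79. So within the accrual scheme, only NS 12 / controls 24 reproduces 95.

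**Step 3. The schedule as run: 24 months per child, NS 12 / controls 24.**
- p = 1 − 0.25 = 0.75 and 1 − 0.50 = 0.50; mean 0.625.
- Events = 95 × 0.625 = 59.4.
- Power = Φ(√59.4 × 0.3466 − 1.96) = 76.1%. The two variants give 74.4% and 74.6%.
- HR detectable with 80% power = exp(2 × 2.8016/√59.4) = about 2.07.
- Evaluable children for 80% = 65.3/0.625 = about 105.
- 100 children with no loss: 62.5 events, 78.2%.

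With events counted only at the two visits, a simulated two-interval log-rank test (48 versus 47 children, 200,000 replicates) gave 74.9%.

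**Step 4. Other readings of the 12-month median, fixed 24 months, 95 children, HR 2.0.**

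| 12-month median belongs to | Event probabilities (NS, controls) | Power, Schoenfeld | Other methods |
|---|---|---|---|
| NS (controls 24) | 0.75, 0.50 | 76% | 75% with two visits |
| Both groups pooled (8.5 and 17) | 0.859, 0.625 | 83% | 80% Freedman |
| Controls (NS 6) | 0.938, 0.75 | 87% | 85% Freedman; 84% with two visits |

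In the pooled row, Freedman's formula with a fixed 24 months returns N = 95.2, which also matches the stated 95.

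**Step 5. The larger cohort.** If 140 NS and 70 controls all complete 24 months, with NS 12 / controls 24, events = 0.75 × 140 + 0.50 × 70 = 140. Power = Φ(√(140 × 2/9) × ln 2 − 1.96) = about 97%, or 96% with two-visit detection.

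**The case against.** The strongest reply is that the article never credits any child with 36 months. The words "followed for 24 months after an accrual period of 12 months" could mean 24 months per child once a 12-month recruitment phase has run, and the next sentence speaks of follow-up over 24 months. A pooled 12-month median with Freedman's formula and exactly the planned follow-up also gives 95. On two of the three readings of the median, the planned schedule meets or roughly meets 80%.

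Much of this stands. A reader might infer that 95 can arise only from 24–36 months per child, and hence that true power is 75–76%. The document does not support that: another route reaches 95, and the group with the 12-month median is never named. What does not fall away is that an accrual period affects the answer only in an accrual-plus-follow-up formula. It is listed among the inputs, and under that formula only NS 12 / controls 24 fits. If follow-up was always a fixed 24 months, the accrual period should not be there.

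A reader might also infer that the study as a whole is underpowered. Step 5 shows otherwise, provided the 210 children complete 24 months. The two-visit issue is likewise minor: it costs about one point of power, Cox software handles ties by standard approximations, and model detail is commonly left to an analysis plan.

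**Conclusion.** The point holds in conditional form. The Phase II power statement uses an accrual-based observation scheme that the schedule does not follow, and it omits which group has the 12-month median. If that group is NS, the 50 + 50 minimum less 5% loss has about 76% power at HR 2.0 (about 75% with events seen only at visits), a shortfall of four to five points, equivalent to a detectable HR of about 2.07. If the median is pooled, power is about 80–83%; if it belongs to controls, about 85–87%. All figures assume exponential event times and take the article's event definition at face value. The effect is small and confined to the Phase II justification for a secondary objective.

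**What to change.** In the Phase II part of Sample size calculation:
- name the group to which the 12-month median applies, and give the implied median in the other group;
- base the calculation on a fixed 24 months per child and remove the accrual period as an input, or state that observation continues to a common closing date if that is intended;
- name the formula and restate the power of the 50 + 50 minimum after 5% loss. If NS has the 12-month median, this is about 75–76% at HR 2.0, or 80% at about HR 2.07.

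Optionally, state that cIMT progression detected only at the 12- and 24-month visits will be analysed with a grouped-time proportional hazards model (complementary log-log link, intervals 0–12 and 12–24 months). It estimates the same hazard ratio and suits the two-visit data.

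The cost is a few sentences of text, with no extra children or visits.

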##### Method

The normal arterial wall is composed by two acoustic impedance interfaces: the transition between blood and intima, and the transition between media and adventitia. The distance between those two acoustic interfaces is the definition for IMT. Thus the cIMT will be defined by determining the thickness between the lines of Pignoli on B-mode ultrasound; with the first echogenic line representing the lumen intima interface, and the second line representing the media-adventitia interface. In addition, a high precision determination of the IMT on B mode Ultrasound with RFQIMT echo tracking will be the reference standard technique for IMT determination [This method has a minimum resolution of 21 μm with ability to measure change in diameters with 1.7-μm spatial resolution as against pure video imaging with a spatial resolution of 150 μm [22].

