##### Quality control

30 patients (15 nephrotic and 15 controls) will be revaluated and their IMT reassessed by a second ultrasonographer, in order to assess inter- and intra-observer variability to have an acceptable variation < 9%.2.MicrovascularII.Nailfold Video capillaromicroscopy Equipment & Method

Nailfold videocapillaroscope with a minimum 300X magnification with digital output [26].

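### The 80% power for cIMT progression rests on a 0.004 mm difference, below the stated resolution and accepted observer variation, with no per-child event defined and no measurement error allowed for

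*Protocol article*

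**What the plan says.** Part B of the protocol's Sample size calculation treats Phase II as a time-to-event comparison with a 12-month median. The quantity being timed is given as "a detectable difference of cIMT of > 0.004 mm over 12 months between children with NS and healthy controls". It then states that "the probability is 80% that the study will detect a difference" at a two-sided 5% level, "if the true hazard ratio is 2.0". The total is 95 children, rounded to 50 with NS and 50 controls, with 12 months of accrual and 24 months of follow-up.

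The cIMT Method section says of the reference radiofrequency technique (RFQIMT): "This method has a minimum resolution of 21" microns. The same sentence gives 1.7 microns for change in diameters and 150 microns for pure video imaging. The cIMT Technique and Endpoint sections average three segments on each side and then the two sides. The cIMT Quality control section requires "inter- and intra-observer variability to have an acceptable variation" below 9%.

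The Statistical analysis section adds that "Cox regression analysis will be applied to analyze the time to event data of the primary or secondary endpoints". Follow-up assessments are at 12 and 24 months.

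**The concern.** There are two problems.

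- **The event is not defined.** A median time, a hazard ratio and a Cox model all need something that happens to one child at one time. The threshold given is a gap between two groups.
- **The threshold is very small.** If it is read as a change within a child, the obvious per-child reading, 4 microns is less than the stated method is said to resolve. The power calculation makes no allowance for misclassified events.

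False events occur in both groups and pull the hazard ratio towards 1. Part B and the Statistical analysis section treat cIMT as the gold standard for progression. A null result could then be reported as no difference in progression, with a claimed 80% power behind it, when the endpoint may have been unable to show one.

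**Working it through.** **1. The plan's own figure.** Inputs from part B: two-sided 5%, 80% power, HR 2.0, 12-month median, 12 months of accrual plus 24 months of follow-up, equal groups. The group to which the median belongs is not stated.

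- Events (Schoenfeld): 4 × (1.960 + 0.842)² / (ln 2)² = 65.3, so 66.
- Event probability with uniform accrual: 1 − [exp(−24λ) − exp(−36λ)] / (12λ). A 12-month median in NS gives 0.820 and a 24-month median in controls gives 0.577; the mean is 0.699.
- N = 66 / 0.699 = 94.5, so 95. Power with 95 × 0.699 = 66.4 events is 80.6%. Adding 5% attrition, 95 / 0.95 = 100, i.e. 50 + 50.

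The stated figure reproduces. With medians of 12 months in controls and 6 in NS, N would be 74. Both versions treat every event as observed without error.

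**2. The threshold against the protocol's own measurement figures.**

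- Resolution: 21 / 4 = 5.25.
- Accepted observer variation: 0.09 × 0.50 mm = 0.045 mm, and 45 / 4 = 11.25. The 0.50 mm is the reported maximum mean in normal children in part A, so 0.045 mm is an upper illustration.
- Averaging: if 21 microns were the SD of one segment reading and six segment errors were independent (both assumptions), the averaged value would have SD 21 / √6 = 8.6 microns, still about twice the threshold.

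**3. False events and power.** No test-retest SD is given, so the error SD per cIMT value is an assumption shown over a range. For a child with no true change, the chance of exceeding 0.004 mm at one visit is 1 − Φ(0.004 / (√2 × SD)). The chance by 24 months counts either visit against a shared baseline.

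Power comes from simulating 48 + 47 children seen at 0, 12 and 24 months. Each has a linear slope such that the error-free time to 0.004 mm is exponential with the stated medians (HR 2.0), capped at 0.02 mm a year. Independent normal error is added at each visit. The event is the first visit with an observed change above 0.004 mm, and the test is the log-rank. Simulation error is one to two percentage points.

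| Error SD (microns) | False event, one visit | False event by 24 months | Power, medians 24 (control) / 12 (NS) | Power, medians 12 / 6 |
|---|---|---|---|---|
| 0 | 0% | 0% | 74% | 85% |
| 1.7 | 5% | 8% | 54% | 64% |
| 4 | 24% | 37% | 27% | 39% |
| 8.6 | 37% | 53% | 13% | 20% |
| 21 | 45% | 61% | 7% | 10% |
| 45 | 48% | 64% | 6% | 6% |

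The 74% with no error is not a measurement effect. The simulation stops at 24 months per child, as the follow-up section does. That gives 95 × (0.75 + 0.50) / 2 = 59.4 events and 76% by the Schoenfeld formula. The loss due to error is the fall from that row.

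**4. The same data as a continuous outcome.** With 47 per group and measurement error only, the difference in mean change detectable with 80% power is 2.80 × √(2/47) × √2 × SD. This is 0.007 mm at SD 8.6 microns, 0.017 mm at 21 and 0.037 mm at 45. True variation between children would raise these figures.

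**The case against.** - **Resolution is not a repeatability SD.** This stands. The 9% is likewise an acceptance ceiling in a quality-control subset, not an expected error. The protocol does not contain the number that fixes the loss, so every power figure above is conditional.
- **The 1.7 micron figure shows that the method can see 4 microns.** This does not stand. The figure is for change in diameters, whereas the endpoint is wall thickness. Even taken as the error SD, it leaves 54 to 64% power.
- **Averaging segments helps.** This stands in part. At 8.6 microns the result depends on the scenario. If controls have no true change and every NS child has gained 0.008 mm by 24 months, the single-visit event probabilities are 0.371 and 0.629. The hazard ratio is ln(0.371) / ln(0.629) = 2.14. With 95 × 0.50 = 47.5 events, power is about 75%. That contrast assumes identical gains within each group, which the plan does not state.
- **The objectives do not rest on this calculation.** This stands. The primary objective is FMD and PORH, secondary objective (a) defines progression by repeat FMD and PORH, and part A justifies 50 + 50 from FMD.

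A reader might infer that the events would be mostly noise, or that 80% power is shown not to be delivered. The documents do not support either as a fact: they define no per-child event and give no SD. Nor is there an arithmetic error in the 95.

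**Conclusion.** The 80% power for cIMT progression is unsupported. It is attached to a group difference rather than a child's event, at a threshold about one fifth of the stated resolution and one eleventh of the accepted observer variation, with no allowance for error. If the threshold is read as a within-child change under HR 2.0, simulated power was below 80% at every nonzero error SD tried: about 54% at 1.7 microns, 27% at 4, 13% at 8.6 and 7% at 21 with medians of 24 and 12 months. The direction is robust. The size rests on the assumed SD, independent normal errors and linear slopes. This should be fixed, but it does not threaten the primary comparison or the minimum of 50 + 50.

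**What to change.** - In part B of the Sample size calculation, remove the 0.004 mm event and the HR 2.0 power statement. In the Statistical analysis section, do not apply Cox regression to cIMT change.
- Compare cIMT change between NS and controls as a continuous outcome at 0, 12 and 24 months in a linear mixed model with group, visit, group × visit and age, using the averaged RFQIMT value.
- Restate the detectable difference from the trial's own repeatability SD, which the rescanning in General protocols and cIMT Quality control will supply.
- If that difference exceeds a plausible 24-month change, report cIMT progression as estimation with confidence intervals only. Keep progression under secondary objective (a) on FMD and PORH, as the protocol already defines it.

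The cost is rewording and a less favourable stated power. No extra children, visits or measurements are needed.
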